**Fig. 1 Fig1:**
[figure not shown]
Schematic timeline of the study. *Key:* *: following randomisation; HIIT: high intensity interval training

### Participants

Men and women previously diagnosed with histologically-confirmed breast, colorectal or prostate cancer (*n* = 226) will be invited to participate.

#### Inclusion criteria

i.≥ 18 years old;ii.≥ 1-month post-treatment for cancer and not anticipating undergoing further treatment during the study period; andiii.Able to travel to the exercise testing and training premises.

#### Exclusion criteria

i.Currently performing any regular HIIT sessions (> 4 sessions in the previous month);ii.The presence of musculoskeletal, neurological, respiratory, metabolic or cardiovascular conditions that may prevent safe completion of the exercise demands of the study; andiii.Participant is pregnant or anticipates becoming pregnant during the study period.

Participants will be required to obtain their doctor’s approval and will be individually screened using a medical history form and interview to confirm eligibility.

#### Discontinuation criteria

Individual participants will be discontinued from the trial, in agreement with the participant’s doctor where appropriate, if:i.The participant is diagnosed with recurrence of cancer and needs to recommence active cancer treatment;ii.It is deemed unsafe for the participant to continue exercising without specialist exercise professional supervision during the unsupervised phase of the trial;iii.The participant has any major surgery or health condition arise within the study period that will significantly affect their ability to participate in exercise for a duration > 1 month;iv.The participant becomes pregnant; orv.The participant elects to withdraw their consent for any reason.

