#### Recruitment and training of peer supporters

Peer supporters, who will also be cancer survivors, will be recruited through CCQ’s existing peer-support network in addition to the aforementioned participant recruitment pathways. Peer supporters will complete the same consent and screening procedures as the study participants. Each peer supporter will undergo CCQ’s peer support training course, delivered over one or two consecutive days (approximately 8 h per day). CCQ’s course helps to equip volunteers with the skills required to provide appropriate emotional support to those affected by cancer, based on their shared experience with cancer either as a patient; the premise of which originates from the Social Cognitive Theory [36]. CCQ’s peer support training is also an opportunity for prospective peer supporters to develop a better understanding of their upcoming role, to ask questions, and to hear from more established volunteers. Course outcomes aim to educate peer supporters on how to support their participant to build motivation, improve confidence and facilitate self-efficacy within the exercising context.

The CCQ peer support training is primarily delivered face-to-face with an accompanying pre-reading package outlining CCQ values, organisational structure, and introductory knowledge of cancer, treatments, and CCQ support services. Information delivered face-to-face utilizes digital presentations, scenario group work, and personal reflections. Moreover, didactics and role play with investigator feedback will be used to enhance the peer supporters’ counselling skills. Peers will also receive training on monitoring participant safety during exercise and what to do should an adverse or serious adverse event occur. An adverse event will be defined as ‘any untoward medical occurrence in a participant subject to the intervention’. A severe adverse event will be defined as ‘any event requiring hospitalisation or causing an inability to carry out usual activities’. Adverse events will be assessed by monitoring and recording during all exercise sessions by the supervising Exercise Physiologist.

Peer supporters will perform the same supervised 4-week HIIT phase as described for the participants to familiarise them with the demands of the prescribed exercise protocol. The supervising AEP uses these sessions to further educate and reiterate to the peer supporters on the specifics of the exercise protocols and safety measures.

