### Randomisation

Following completion of the 4-week supervised training phase and the second testing session, participants will be stratified by sex and age before being randomly assigned (1:1 allocation ratio) to either a peer support group or a non-peer support group. Randomisation will be performed using a computerised random number generator by a research officer independent to the study. Non-systematic block sizes of four, six, or eight will be used to ensure allocation concealment. Randomisation history will be kept secure by the independent research officer in an electronic password-protected file. The independent research officer will confidentially communicate the allocation result to the trial’s primary investigator within 48 h after completing outcome testing following the second testing session. All investigators will be blinded to group allocation for baseline testing, the supervised phase and for testing following the supervised phase, with randomisation occurring after the completion of testing following the supervised phase. The primary outcome will be analysed by a researcher blinded to group allocation. Unblinding will not be permissible under any circumstances. A schematic representation of the study protocol is shown in Fig. 1.

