### Statistical considerations and data analysis

A priori power calculations determined that a sample of *n* = 188 (*n* = 94 per group) will be needed to detect a minimum between-group difference in MVPA levels at 12 months, with 80% power and 5% alpha. To account for an anticipated dropout rate of 20%, 226 participants (*n* = 113 per group) will thus be recruited for this study. A priori criteria for successful provision of peer support will be contacting participants on average on one or more occasions per week over the 12-month maintenance phase.

Data will be assessed for normality of distribution using the Kolmogorov-Smirnov test. Raw continuous data (e.g. minutes of MVPA per day) will be analysed using linear mixed (fixed and random) modeling, to assess changes over time and differences between groups. Group, time, and group × time interaction will be treated as fixed factors; participants will be treated as a random factor with individual intercepts. Each model will include covariates, as appropriate, and will be adjusted using the baseline value as a fixed continuous covariate as previously described by Courneya et al. [113]. Model residuals will be formally assessed for normality by use of the Kolmogorov-Smirnov test and visual inspection of histogram plots. Bonferroni pairwise adjustments will be made for all subsequent comparisons.

Non-continuous data will be analysed with the target distribution and relationship fixed to multinomial logistic regression. Statistical significance will be set at an alpha of *p* < .05 and analyses will be conducted using the intention-to-treat approach. There are no interim analyses planned or early trial termination guidelines. Data from the peer supporters will be analysed separately to those of the participants.

Qualitative data from the semi-structured interview transcripts will be assessed using inductive thematic analysis. Codes will be assigned to salient text segments across the entire data set, before codes will be combined to define overarching themes [108].

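### Clinical discontinuation takes randomised participants out of the trial altogether, with no stated outcome follow-up, which undermines the intention-to-treat aim

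*Protocol article*

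**What the plan says.** The Discontinuation criteria section opens: "Individual participants will be discontinued from the trial", with the doctor's agreement where that is appropriate. Five reasons follow. The first is "The participant is diagnosed with recurrence of cancer and needs to recommence active cancer treatment". The second is "It is deemed unsafe for the participant to continue exercising without specialist exercise professional supervision during the unsupervised phase of the trial". The third is major surgery or a new health condition that "will significantly affect their ability to participate in exercise for a duration > 1 month". The fourth is pregnancy and the fifth is withdrawal of consent. All five share one consequence, which is leaving the trial; stopping the exercise or the peer contact is not named as a separate step.

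The Randomisation section places allocation after the supervised phase, "with randomisation occurring after the completion of testing following the supervised phase". The second criterion is tied to the unsupervised phase and so applies only after randomisation. The others can also occur then.

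Study design says that every participant is assessed at baseline, at the end of the supervised phase, and at 3, 6 and 12 months. The primary outcome is MVPA at 12 months. Statistical considerations and data analysis specifies a linear mixed model with a random intercept per participant and says that "analyses will be conducted using the intention-to-treat approach". The only contact described for people who leave early is an invitation to interview (Semi-structured interviews).

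**The concern.** Intention-to-treat aims at the effect of allocation in everyone randomised, which requires outcomes on everyone as far as they can be had. Here the protocol's own rule ends participation for some randomised people, for reasons close to the outcome. The third criterion is triggered by reduced ability to exercise, and the outcome is how much moderate-to-vigorous activity a person does. Their unseen 12-month values are therefore plausibly low.

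A random-intercept mixed model handles missing values under missing at random, meaning that the observed data explain the missingness. Activity recorded before a recurrence or an operation may say little about activity after it. The same gap affects the quality-of-life outcomes and the QALYs in the economic evaluation. A statistical analysis plan cannot repair this later, because it cannot recover outcomes that were never collected.

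**Working it through.** **Side by side.** Study design has all participants assessed to 12 months. Discontinuation criteria takes some of them out of the trial before then. Statistical considerations promises intention-to-treat. No section says that outcome assessment continues after discontinuation, and none says that data already collected are discarded or that these participants leave the analysis set.

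**The plan's own figure.** 188 evaluable participants with 20% dropout: 188 × 1.20 = 225.6, rounded up to 226, which matches. The 188 cannot be checked because no difference or SD is given. With two-sided 5% alpha (sidedness assumed), 80% power and 94 per group, the implied standardised difference is d = (1.960 + 0.842) × √(2/94) = 0.409. This is back-solved and is used only as a scale.

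**Illustration.** The following inputs are assumed; none is in the article.

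- Continuers differ by d between arms.
- Discontinued participants in both arms lie g SD below control continuers, with no peer-support benefit; g = 0.5 to 1.0.
- The proportions discontinued are q_p (peer support) and q_c (control).

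Difference in all randomised = (1 − q_p)d − (q_p − q_c)g.
Difference in continuers only = d.
Overstatement = q_p·d + (q_p − q_c)g.

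*Equal rates, d = 0.409* (g cancels):

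| Discontinued per arm | All randomised | Continuers | Overstatement |
|---|---|---|---|
| 5% | 0.95 × 0.409 = 0.388 | 0.409 | 0.020 |
| 10% | 0.90 × 0.409 = 0.368 | 0.409 | 0.041 |
| 20% | 0.80 × 0.409 = 0.327 | 0.409 | 0.082 |

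*Equal rates, no true effect (d = 0):* the overstatement is 0.

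*Unequal rates, no true effect:* (q_p − q_c)g in size. For 5% v 10% this is 0.05 × 0.5 = 0.025 to 0.05 × 1.0 = 0.050 SD. For 10% v 20% it is 0.10 × 0.5 = 0.050 to 0.10 × 1.0 = 0.100 SD. The bias favours the arm that loses more participants.

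*Unequal rates, d = 0.409:* with 10% lost in the peer arm and 5% in control, the overstatement is 0.041 + 0.025 = 0.066 to 0.041 + 0.050 = 0.091 SD. With the rates reversed it is 0.020 − 0.025 = −0.005 to 0.020 − 0.050 = −0.030 SD, an understatement. The sign depends on which arm loses more.

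These figures compare continuers with all randomised. They ignore the baseline adjustment and the earlier repeated measures, which would absorb part of any gap.

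**The case against.** The strongest reply is that this is ordinary missing data in a condensed article. Intention-to-treat means analysing people in the arm to which they were randomised, and nothing here prevents that. Any 3- and 6-month data from people who later discontinue enter the mixed model. The article does not say in terms that follow-up stops, and the full protocol may say more.

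Much of this stands. A reader might infer that the rule contradicts intention-to-treat or deletes low-activity outcomes. The text supports neither: no data are deleted, no one is excluded from the analysis set, and low activity after discontinuation is a plausible inference, not a stated fact. Nor is the rule as broad as relapse or surgery in general. Recurrence counts only if treatment must restart, and surgery or illness only if exercise is significantly limited for more than a month.

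A reader might also infer that discontinuation will be detected more often in the peer arm, because "Peers will also receive training on monitoring participant safety during exercise" and peers keep weekly contact. That is speculative. Research staff monitor sessions in both arms (12-month maintenance phase), medical status and hospital admissions are recorded at every assessment (Outcomes), and the research team records adverse events. Recurrence needing treatment, major surgery and pregnancy do not depend on a peer noticing them. At most the second criterion, which is a judgement, could be affected.

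What does not stand is the reading of this as mere silence. The article states a rule, ends participation in the trial under it, and gives clinical events the same consequence as withdrawn consent.

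**Conclusion.** The point holds in a limited form. Followed as written, the rule loses 12-month MVPA, quality of life and AQoL-8D for some randomised participants, for reasons tied to being unable to exercise. This undermines the intention-to-treat aim and sits badly with the statement that all participants are assessed. The missing-at-random assumption may not hold for these people.

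The size is unknown. In the illustration, 10% discontinuation in both arms gives 0.37 SD in all randomised against 0.41 SD in continuers. That rests on an assumed rate, a back-solved difference and the assumption that benefit is confined to continuers. Equal rates with no true effect produce no bias. Unequal rates could bias in either direction, but the documents give no basis for expecting them. Quoting a bias as a percentage of the trial's target would be unsound, since no target difference is stated. This is a cheap improvement and does not invalidate the design.

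**What to change.** Leave the clinical criteria untouched. Reconcile Study design, Discontinuation criteria and Statistical considerations by stating that discontinuation under the first four criteria does not end outcome follow-up, and by treating withdrawal of consent for follow-up as a separate event. Unless that consent is withdrawn, continue accelerometry and questionnaires at 3, 6 and 12 months and include the results in the intention-to-treat analysis under the assigned arm. Neither measure needs an exercise test.

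The cost is a short wording change in the protocol and consent form, and a small follow-up effort for what should be a few participants.

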### Recruitment

#### Participant recruitment

Participants will be recruited from the University of Queensland, by way of media releases, presentations, advertisements in newsletters, newspapers, social media and noticeboards. Participants will also be recruited via the Cancer Council Queensland (CCQ) support group network, CCQ [name] telephone support service, CCQ Registries and the Queensland Health Cancer Registry. Potential participants, after meeting the eligibility criteria and being advised of the study requirements by the principal investigator, will receive the Participant Information Sheet, Participant Consent Form, Medical History Form and Medical Doctor Consent Form. Each will then be contacted by telephone by the principal investigator to discuss any questions they may have regarding the trial. If they wish to continue they will be required to obtain their Doctor’s written consent and sign the Participant Consent Form, both of which will be collected and securely stored by the primary investigator.

#### Recruitment and training of peer supporters

Peer supporters, who will also be cancer survivors, will be recruited through CCQ’s existing peer-support network in addition to the aforementioned participant recruitment pathways. Peer supporters will complete the same consent and screening procedures as the study participants. Each peer supporter will undergo CCQ’s peer support training course, delivered over one or two consecutive days (approximately 8 h per day). CCQ’s course helps to equip volunteers with the skills required to provide appropriate emotional support to those affected by cancer, based on their shared experience with cancer either as a patient; the premise of which originates from the Social Cognitive Theory [36]. CCQ’s peer support training is also an opportunity for prospective peer supporters to develop a better understanding of their upcoming role, to ask questions, and to hear from more established volunteers. Course outcomes aim to educate peer supporters on how to support their participant to build motivation, improve confidence and facilitate self-efficacy within the exercising context.

The CCQ peer support training is primarily delivered face-to-face with an accompanying pre-reading package outlining CCQ values, organisational structure, and introductory knowledge of cancer, treatments, and CCQ support services. Information delivered face-to-face utilizes digital presentations, scenario group work, and personal reflections. Moreover, didactics and role play with investigator feedback will be used to enhance the peer supporters’ counselling skills. Peers will also receive training on monitoring participant safety during exercise and what to do should an adverse or serious adverse event occur. An adverse event will be defined as ‘any untoward medical occurrence in a participant subject to the intervention’. A severe adverse event will be defined as ‘any event requiring hospitalisation or causing an inability to carry out usual activities’. Adverse events will be assessed by monitoring and recording during all exercise sessions by the supervising Exercise Physiologist.

Peer supporters will perform the same supervised 4-week HIIT phase as described for the participants to familiarise them with the demands of the prescribed exercise protocol. The supervising AEP uses these sessions to further educate and reiterate to the peer supporters on the specifics of the exercise protocols and safety measures.

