## Methods

### Study design

This two-arm randomised controlled trial will involve men or women with a previous diagnosis of breast, colorectal or prostate cancer. All participants and peer supporters will first complete 4 weeks (12 sessions) of HIIT supervised by Accredited Exercise Physiologists (AEP) at the School of Human Movement and Nutrition Sciences, The University of Queensland, Brisbane, Australia (‘supervised phase’). On completion of the supervised phase, participants will be stratified by gender and age before being randomly assigned (1:1) to either a peer support group or a non-peer support group. All will be provided with written recommendations to maintain three HIIT sessions per week, or an alternative equivalent that meets the exercise oncology guidelines (i.e. 150 min per week of moderate or 75 min per week of vigorous aerobic exercise or an equivalent combination), for 12 months [21, 22]. Those assigned to the peer support group will have access to a peer who will provide support to meet the HIIT and/or exercise guidelines.

All participants will complete a series of assessments (see Table 1) at baseline, at the end of the supervised phase, and at 3-, 6- and 12-months following the supervised phase (see Fig. 1).

**Table 1 Tab1:** Schedule of data collection

Assessment or Outcome	Study Period						
*Time Point:*	*Pre-FM*	*FM*	*Pre-SP*	*Post-SP*	*3 M*	*6 M*	*12 M*
*Screening*							
Participant eligibility	✓						
Adult Pre-Exercise Screening System	✓						
Informed consent	✓						
Doctor’s consent	✓						
Medical history and current status	✓	✓	✓	✓	✓	✓	✓
Demographics	✓						
Concomitant research study participation	✓	✓	✓	✓	✓	✓	✓
*Primary Outcomes*							
Moderate-to-vigorous physical activity (MVPA)			✓	✓	✓	✓	✓
*Secondary Outcomes*							
Cardiorespiratory fitness ($$ \dot{\mathrm{V}}{\mathrm{O}}_{2\mathrm{peak}} $$)		✓	✓	✓	✓	✓	✓
Body composition (DXA)			✓	✓	✓	✓	✓
Anthropometry (BMI)			✓	✓	✓	✓	✓
Strength (isometric grip strength)			✓	✓	✓	✓	✓
Blood biomarkers (IL-6, IL-8, Hepcidin, TNF-α, IGF-1, IGF-2, IGFBP-3 and CRP)			✓	✓	✓	✓	✓
Self-reported physical activity (Godin)			✓	✓	✓	✓	✓
Sedentary behaviour and light physical activity (accelerometry)			✓	✓	✓	✓	✓
Quality of life and wellbeing (EORTC QLQ C-30, SF-36 and FACT-G)			✓	✓	✓	✓	✓
Cancer-related fatigue (FACIT-F)			✓	✓	✓	✓	✓
Insomnia (ISI)			✓	✓	✓	✓	✓
Symptom distress (BSI)			✓	✓	✓	✓	✓
Depression and anxiety (DASS, PHQ-9 and GAD-7)			✓	✓	✓	✓	✓

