Participant:peer supporter relationship (Therapeutic Alliance)			✓	✓	✓	✓	✓
Self-efficacy			✓	✓	✓	✓	✓
Barriers and enablers to PA			✓	✓	✓	✓	✓
Tertiary Outcomes							
Semi-structured interviews							✓
Physical activity preferences			✓	✓	✓	✓	✓
Economic evaluation (AQoL-8D)			✓	✓	✓	✓	✓
Adverse and serious adverse events		✓	✓	✓	✓	✓	✓

*Key: Pre-FM* pre-familiarisation, *FM* familiarisation, *Pre-SP* pre-supervised phase, *Post-SP* post-supervised phase, *3 M* 3-months post-randomisation testing, *6 M* 6-months post-randomisation testing, *12 M* 12-months post-randomisation testing, $$ \dot{\mathrm{V}}{\mathrm{O}}_{2\mathrm{peak}} $$ peak volume of oxygen consumption, *DXA* dual energy X-ray absorptiometry, *BMI* body mass index, *IL-6* interleukin 6, *IL-8* interleukin 8, *TNF-α* tumour necrosis factor – alpha, *IGF-1* insulin-like growth factor 1, *IGF-2* insulin-like growth factor 2, *IGFBP-3* insulin-like growth factor-binding protein 3, *CRP* C-reactive protein, *Godin* Godin Leisure-Time Physical Activity Questionnaire, *EORTC QLQ C-30* European Organization for Research and Treatment of Cancer quality of life questionnaire for people with cancer, *SF-36* Short form 36 health survey, *FACT-G* Functional Assessment of Cancer Therapy: General, *FACIT-F* The Functional Assessment of Chronic Illness Therapy: Fatigue, *ISI* Insomnia Severity Index, *BSI* Brief Symptom Inventory, *DASS* Depression Anxiety Stress Scale, *PHQ-9* Patient Health Questionnaire-9, *GAD-7* Generalised Anxiety Disorder 7-item scale, *PA* physical activity, *AQoL-8D* Assessment of Quality of Life – 8 Dimensions Multi-Attribute Utility Instrument

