### Peer support intervention

Participants randomised to the peer support group will be assigned a peer supporter. Assignment will be determined by training time availability and preference to enhance the ease of scheduling face-to-face exercise sessions. The peer supporter will maintain weekly contact (by phone, email and/or joining training sessions) with their participant for the 12-month maintenance phase. Contact frequency and type will be diarised by the peer supporter following each occurrence. The peer supporter’s goal will be to encourage their participant to maintain physical activity levels throughout the 12-month training period, equivalent to those achieved during the supervised phase. Peer supporters will be encouraged to use the knowledge and strategies gained from the CCQ peer support training sessions during discussions with their participants i.e. goal setting and planning, facilitating self-efficacy, improving confidence, overcoming barriers and building motivation. Where peer supporters have difficulty maintaining the recommended weekly contact regime, they will be encouraged to notify the research team to discuss and apply appropriate strategies moving forward. Participants will be required to diarise each exercise training session. Cycle ergometers will record each exercise session and data will be periodically retrieved by the researcher team. The training diaries and cycle ergometer data, in conjunction with the accelerometer data, will be used to assess maintenance to physical activity and the prescribed exercise over the 12 months.

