### Outcomes

Primary and secondary outcomes will be measured at baseline, at the end of the 4-week supervised phase, and at 3-, 6- and 12-months following the supervised phase. See Table 1 for a visual representation of the data collection schedule.

Assessments will be performed in a consistent order to allow for appropriate rest periods and to ensure that successive outcomes are minimally influenced by accumulative testing-fatigue. Participants will be advised to take prescribed medications as normal throughout the study period. Concomitant study participation will be documented at each testing session and the primary investigator will determine whether any co-intervention bias may influence the trial outcomes. Hospital admissions and any alterations in medical status or medications will be recorded at each assessment for future reference during analysis of results.

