#### Adverse and serious adverse events

To assess the efficacy of the intervention, adverse events will be recorded by the research team immediately upon their notification. An adverse event will be defined as ‘any untoward medical occurrence in a participant subject to the intervention’. A severe adverse event will be defined as ‘any event requiring hospitalisation or causing an inability to carry out usual activities’. In the occurrence of any adverse or serious adverse event, the research team will report to the governing ethics committee, review relevant risk assessments, aim to mitigate future risk of adverse events and provide the appropriate duty of care to the participant/s concerned.

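### The physiologist-based adverse-event rule cannot operate after randomisation, and only the peer arm then has a safety-trained weekly contact, so by-arm counts pooled over all sources are at risk of differential ascertainment

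*Protocol article*

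**What the plan says.** The article describes adverse-event capture in several places.

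- **Recruitment and training of peer supporters:** "Adverse events will be assessed by monitoring and recording during all exercise sessions by the supervising Exercise Physiologist". The same section says "Peers will also receive training on monitoring participant safety during exercise and what to do should an adverse or serious adverse event occur".
- **Adverse and serious adverse events (tertiary outcomes):** "adverse events will be recorded by the research team immediately upon their notification". This section gives the purpose of recording as assessing the efficacy of the intervention.
- **Table 1:** the row "Adverse and serious adverse events" is ticked at familiarisation, before and after the supervised phase, and at 3, 6 and 12 months. The schedule covers both arms: "All participants will complete a series of assessments (see Table 1) at baseline, at the end of the supervised phase", and at the later visits.
- **Outcomes:** "Hospital admissions and any alterations in medical status or medications will be recorded at each assessment".
- **Randomisation:** "Following completion of the 4-week supervised training phase and the second testing session, participants will be stratified by sex and age" and then allocated.
- **Peer support intervention:** "The peer supporter will maintain weekly contact (by phone, email and/or joining training sessions) with their participant" throughout the 12-month maintenance phase.

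The discontinuation criteria describe the phase after the 4 weeks as unsupervised.

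**The concern.** The physiologist rule is worded to cover every exercise session, yet a physiologist supervises only the 12 sessions that precede randomisation. Read literally, it promises session-level recording during the very months in which no supervising physiologist is present. The section on adverse events gives a different rule, recording on notification, and the two are not reconciled.

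A rule driven by notification depends on who notices an event and passes it on. In the peer arm a supporter trained on adverse events is in touch every week and may be at the session. The control arm has no counterpart. If supporters pass events on, more of the peer arm's events will reach the record at the same true risk.

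Adverse events are a listed outcome, so even descriptive counts by arm will be read as a comparison. What is at stake is an apparent excess under peer support that partly reflects better detection.

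**Working it through.** The article states no figure on this point, so there is none to reproduce. The first step sets the capture routes side by side.

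| Route | Where stated | Works after randomisation? | Peer arm | Control arm |
|---|---|---|---|---|
| Supervising physiologist | Recruitment and training of peer supporters | No; supervision ends with the 4 weeks | – | – |
| Adverse-event row at 3, 6 and 12 months | Table 1 | Yes | Yes | Yes |
| Hospital admissions, medical status, medications | Outcomes | Yes, each assessment | Yes | Yes |
| Notification to the research team | Adverse and serious adverse events | Yes | Yes | Yes |
| Trained weekly contact | Recruitment and training of peer supporters; Peer support intervention | Yes | Yes | No |

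The ergometer and heart-rate data described under 12-month maintenance phase exist for both arms but are not described as adverse-event capture.

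The arms therefore share a common floor of capture, and the peer arm has one possible addition. The intervals between post-randomisation assessments are 3, 3 and 6 months, so the addition matters most for events mild or short enough to be forgotten by the next visit.

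The second step asks how large the distortion could be. All inputs are assumptions except the 113 per group from the sample-size paragraph:

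- true risk p, equal in both arms: 0.10 to 0.40
- c0, the share of events captured by the shared routes: 0.3, 0.6, 0.9 or 1.0
- e, the share of otherwise missed events that peer supporters pass on: 0.25 or 0.50

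Peer-arm capture is c1 = c0 + (1 − c0) × e. The apparent risk ratio is (p × c1)/(p × c0) = c1/c0, which does not depend on p.

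| c0 | c1 at e = 0.25 | Ratio | c1 at e = 0.50 | Ratio |
|---|---|---|---|---|
| 0.3 | 0.3 + 0.7 × 0.25 = 0.475 | 1.58 | 0.3 + 0.7 × 0.50 = 0.65 | 2.17 |
| 0.6 | 0.6 + 0.4 × 0.25 = 0.70 | 1.17 | 0.6 + 0.4 × 0.50 = 0.80 | 1.33 |
| 0.9 | 0.9 + 0.1 × 0.25 = 0.925 | 1.03 | 0.9 + 0.1 × 0.50 = 0.95 | 1.06 |
| 1.0 | 1.00 | 1.00 | 1.00 | 1.00 |

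If supporters pass on nothing (e = 0), c1 = c0 and the ratio is 1.00 at any c0.

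If someone tested the two proportions at two-sided 0.05 with 113 per arm (normal approximation, pooled variance under the null), the chance of a spurious significant peer-arm excess would be about 3–5% at c0 = 0.9, 5–27% at c0 = 0.6 and 10–77% at c0 = 0.3, across the assumed p and e. Without differential capture it would be 2.5% in that direction. The article plans no such test, so these figures only show how sensitive a comparison would be.

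**The case against.** A reader might infer that the trial's safety comparison is biased against peer support, or that control events have no reliable route to the record. The documents do not support either reading.

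- Table 1 schedules adverse-event assessment at 3, 6 and 12 months for everyone, and hospital admissions and medical changes are recorded at each assessment. Events that lead to admission are sought equally in both arms.
- No formal between-arm test of adverse events is described, nor any rule that pools events across sources. Tabulation is commonly left to the analysis plan, which is not shown.
- No duty on peer supporters to report events to the team is stated. They are trained in what to do, but the diary described covers contact frequency and type. It would be wrong to count about 52 weekly contacts as 52 reporting occasions. Controls can also notify the team directly.
- Nothing in the article indicates poor capture at visits, and the larger ratios above need it.
- The physiologist sentence can be read as applying only where a physiologist is supervising.

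Most of this stands, and it reduces the point from a shown bias to a risk. Two things remain. The sentence claims all sessions and conflicts with the unsupervised phase as written. And equal visits set a shared floor; they do not remove the extra possible route in one arm.

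**Conclusion.** The point holds as a risk of differential ascertainment. The physiologist rule cannot apply after randomisation, and the text should be reconciled with the unsupervised phase. Pooled counts could then be higher in the peer arm at equal true risk, mainly through minor or transient events between visits.

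The direction rests on the assumption that supporters pass on some events that would otherwise be missed. The size is unknown: no excess if the shared routes capture everything, 3–6% if they capture 90%, and roughly a doubling only if they capture as little as 30% and supporters relay half of the rest. Serious events are less affected. The primary outcome is not touched. This is a worthwhile, inexpensive improvement to a tertiary outcome.

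**What to change.** 1. Limit the physiologist sentence to the supervised phase, and refer to Table 1 and the notification rule for the maintenance phase.
2. Base any between-arm adverse-event comparison on events elicited with the same structured question at the 3-, 6- and 12-month visits in both arms.
3. Record the source of every event (visit, participant, peer supporter).
4. List events known only through peer supporters separately, outside the comparison. All events continue to be recorded, reported and acted on exactly as the adverse-event section requires.

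The cost is one field on the adverse-event form and a few lines of protocol and analysis-plan wording, with no extra visits or staff. There are two drawbacks. Some mild events leave the comparison, though they stay in the listings. Weekly contact may also help peer-arm participants recall events at visits, so the asymmetry is reduced and not fully removed.
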